### Sample size

This is an exploratory study; no prior data exists for neuroprotection as the primary outcome in POAG with Ayurveda intervention. A minimum of 50 participants will be enrolled in total, with 30 participants assigned to the intervention group and 20 participants assigned to the control group.

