**Figure 1. f1:**
[figure not shown]
Activity chart. Study design flow chart illustrating the participant activity. Participants were screened and assessed for eligibility, then randomized into two groups: Group A (Control) and Group B (Trial). Assessments will be conducted in baseline, 30, 60, and 90 days during the 3-month intervention period, with a follow-up of 180 days.

**Table 4. T4:** Participant timeline.

Parameter	Instrument	Screening	Baseline	30 days	60 days	90 days (End Tx)	180 days (Follow-up)
Informed consent	Consent form	+					
Demographic and medical history	Case report form	+					
Clinical examination	As per need	+	+				
Assessment of ADR	ADR reporting form			+	+	+	+
Assessment of drug compliance	Compliance chart			+	+	+	
Issue of trial drugs	Trial drug kit		+	+	+		
Visual acuity (distant & near)	ETDRS LogMAR Chart	+	+	+	+	+	+
Automated VF testing (30–2 SITA standard)	ZEISS Humphrey Field Analyzer 3 (HFA)	+	+	+	+	+	+
Retinal Nerve Fiber Layer (RNFL) Thickness	ZEISS CIRRUS HD-OCT	+	+	+	+	+	+
Intraocular Pressure (IOP)	Goldmann Applanation Tonometer/Non-Contact Tonometer (NCT)	+	+	+	+	+	+
Central Corneal Thickness (CCT)	TOPCON Pachymeter/ZEISS CIRRUS HD-OCT	+	+	+	+	+	+
CBC with ESR, FBS, KFT, LFT	Standard Clinical Laboratory Tests		+	–	–	+	–

ADR – adverse drug reaction, CBC – complete blood count, CCT – central corneal thickness, ETDRS – early treatment diabetic retinopathy study, ESR – erythrocyte sedimentation rate, FBS – fasting blood sugar, HFA – humphrey field analyzer, IOP – intraocular pressure, KFT – kidney function test, LFT – liver function test, LogMAR – logarithm of the minimum angle of resolution, NCT – non-contact tonometer, OCT – optical coherence tomography, RNFL – retinal nerve fiber layer, VF – visual field.

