### Data management

Data entry is conducted by PI using verification procedures, with all information recorded in a password-protected electronic database. Each participant is assigned a unique study ID, and direct identifiers are stored separately from the clinical dataset. The electronic database is accessible only to authorized personnel, and all physical documents (CRFs) are kept in locked cabinets at the study site. To ensure data quality, built-in range checks and validation rules automatically flag any out-of-range or inconsistent entries (Microsoft® Excel® for Microsoft 365 MSO (Version 2503 Build 16.0.18623.20076) 64-bit).

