### Statistical methods

Within each group, repeated-measures analysis of variance (RM-ANOVA) or a suitable post-hoc test will be employed to analyze continuous variables, including LogMAR acuity, visual field index (VFI), MD, pattern standard deviation (PSD), RNFL thickness, IOP, and central corneal thickness (CCT) depending on the normality of distribution. Between-group comparisons will be performed using the unpaired t-test or its nonparametric alternatives as needed. Laboratory parameters such as complete blood count (CBC), erythrocyte sedimentation rate (ESR), fasting blood sugar (FBS), kidney function test (KFT), and liver function test (LFT) will be assessed via paired t-tests for within-group changes and unpaired t-tests for between-group differences. All statistical analyses will be conducted using IBM SPSS Statistics (Version 29) or later.

The primary analysis follows the intention-to-treat (ITT) principle, incorporating all randomized participants who have received at least one dose of the allocated intervention. Missing data, when deemed missing at random, may be addressed using multiple imputation based on observed participant characteristics. A per-protocol (PP) analysis will also be performed among participants who strictly adhere to the intervention, serving as a sensitivity assessment to confirm the robustness of the results.

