### Interim analyses

No interim analyses are planned due to the exploratory design and modest sample size. However, if substantial safety concerns emerge or a high incidence of serious adverse events appears to be associated with the study intervention, early termination may be considered.

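### The only laboratory analysis the article names is t-tests on means, which are nearly blind to toxicity in a few of 30 treated participants

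*Protocol article*

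**What the plan says.** Under Statistical methods, the laboratory parameters (CBC, ESR, FBS, KFT, LFT) "will be assessed via paired t-tests for within-group changes and unpaired t-tests for between-group differences". No count of abnormal values, shift from baseline or individual listing is named beside the t-tests. The sentence before it, on the other continuous variables, allows a fallback: "Between-group comparisons will be performed using the unpaired t-test or its nonparametric alternatives as needed". The laboratory sentence does not repeat that option.

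Table 4 (Participant timeline) schedules "CBC with ESR, FBS, KFT, LFT" at baseline and 90 days only. The Sample size section fixes the arms, "with 30 participants assigned to the intervention group and 20 participants assigned to the control group".

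Other sections touch on safety in individuals:
- Table 4 has adverse drug reaction assessment at 30, 60, 90 and 180 days.
- The section on discontinuing or modifying interventions leaves pausing or stopping to the investigator, case by case, with a record in the case report form.
- Data monitoring provides for periodic review by an internal group.
- Adverse events reporting sends events to the national pharmacovigilance centre.
- Interim analyses allows early termination to be considered "if substantial safety concerns emerge or a high incidence of serious adverse events appears to be associated with the study intervention".
- Data management mentions that "built-in range checks and validation rules automatically flag any out-of-range or inconsistent entries", and gives data quality as the purpose.

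None of these is described as an analysis of laboratory values by arm.

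**The concern.** These tests are the only scheduled laboratory safety data for an oral product that contains mineral nanoparticles. Injury to liver, kidney or blood usually shows as a few participants far outside the reference range, not as a shift of the whole group. A t-test divides the mean change by its standard error, and a few extreme values raise both together. The statistic is therefore capped when few people are affected, however abnormal they are.

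At stake is the safety statement in the final report. Followed as written, the analysis could support a statement that liver or kidney function did not change significantly while several treated participants were clearly abnormal.

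**Working it through.** The article gives no power, alpha or detectable difference for the laboratory data, so there is no stated figure to reproduce.

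**Inputs from the article.** n = 30 intervention and m = 20 control (Sample size); paired and unpaired t-tests (Statistical methods); one change per participant, baseline to day 90 (Table 4).

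**Assumptions.** Two-sided alpha 0.05 (not stated; range below). Changes in unaffected participants are normal with SD 1. In k treated participants the value rises by a further X SD. No control is affected.

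**1. Limit as X grows.**
- Paired, n = 30: t tends to √[k(n−1)/(n−k)]; the critical value on 29 df is 2.045. For k = 1, √(29/29) = 1.00. For k = 3, √(87/27) = 1.80.
- Pooled unpaired: t tends to (k/n) / √{[k(n−k)/n]/(n+m−2) × (1/n+1/m)}; the critical value on 48 df is 2.011. For k = 1, 0.0333/√(0.9667/48 × 0.0833) = 0.81.

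| Affected of 30 | Paired t | p | Pooled t | p |
|---|---|---|---|---|
| 1 | 1.00 | 0.33 | 0.81 | 0.42 |
| 2 | 1.44 | 0.16 | 1.17 | 0.25 |
| 3 | 1.80 | 0.083 | 1.46 | 0.15 |
| 4 | 2.11 | 0.043 | 1.72 | 0.09 |
| 5 | 2.41 | 0.023 | 1.96 | 0.056 |
| 6 | 2.69 | 0.012 | 2.19 | 0.033 |

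These limits do not depend on the analyte's mean or SD. With extreme values, up to 3 affected (paired) or 5 (pooled) end non-significant. With unequal variances (Welch), the limiting t equals the paired one. At alpha 0.10 the largest numbers that still end non-significant are 2 (paired) and 3 (pooled); at 0.01 they are 6 and 8.

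**2. Finite values.** Chance of p<0.05, 40,000 simulated trials per cell:

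| Test | Affected | 3 SD | 5 SD | 10 SD | 20 SD | 50 SD |
|---|---|---|---|---|---|---|
| Paired | 1 | 4.8% | 4.1% | 1.0% | 0.0% | 0.0% |
| Paired | 2 | 8.3% | 8.4% | 3.6% | 0.1% | 0.0% |
| Paired | 3 | 14.5% | 17.9% | 15.5% | 5.5% | 0.0% |
| Paired | 4 | 24.2% | 34.9% | 48.5% | 61.7% | 84.9% |
| Pooled | 1 | 4.2% | 3.4% | 1.2% | 0.0% | 0.0% |
| Pooled | 2 | 5.9% | 5.4% | 2.0% | 0.0% | 0.0% |
| Pooled | 3 | 8.6% | 9.2% | 5.2% | 0.4% | 0.0% |
| Pooled | 4 | 12.7% | 15.5% | 13.8% | 4.8% | 0.0% |

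With 2 or 3 affected, detection first rises to a low peak and then falls to zero. With 1 to 3 affected, the highest value over all the tests tried is about 18% (17.9% paired; 18.3% Welch, at 10 SD).

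**3. What counting would show.** The chance of at least one case among 30 is 1 − (1−π)^30. This gives 60%, 79% and 96% for true rates π of 3%, 5% and 10%. A significance test on the counts would not help: Fisher's exact test against 0/20 gives p = 0.069 at 6/30 and first falls below 0.05 at 7/30 (p = 0.033).

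**The case against.** The strongest reply is that this rests partly on silence. The article does not call the t-tests the whole safety analysis, ties no safety conclusion to a p-value, and may leave shift tables and listings to an analysis plan that is not shown. That stands as far as it goes: the absence of such tables is no fault in a condensed article. What remains is that the one laboratory method it does fix is poorly suited to its purpose.

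Second, individual toxicity has other routes: adverse reaction forms, investigator discretion to stop, pharmacovigilance reporting and internal review. This also stands. A reader might infer that the trial has no other means of noticing organ toxicity, and the documents do not support that. But these routes concern surveillance of individuals and do not supply a laboratory result by arm. The range checks are a data-quality measure at entry.

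Third, a reader might infer that t-tests always become less sensitive as abnormal values grow. They do not. With 4 of 30 affected, paired detection rises from about 24% at 3 SD to 85% at 50 SD, and from 6 of 30 the pooled test also becomes significant when values are large enough.

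Fourth, the nonparametric option might be read as covering laboratory data. It would not rescue the analysis: with 3 of 30 at 400 U/L (assumed baseline mean 25, SD 8, change SD 8), the Wilcoxon test reached p<0.05 in 11% of trials and the Mann-Whitney test in 7%.

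A reader might also count chance positives across many analytes. The article does not give the number of analytes, so no such figure is offered here.

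**Conclusion.** The point holds in a limited form. With 30 v 20, the named laboratory tests are nearly blind to toxicity in 1 to 3 treated participants: at most about an 18% chance of p<0.05, falling to zero with extreme values. The pooled between-group test can miss up to 5 of 30. A statement of no significant change would therefore not be evidence of laboratory safety.

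The closed-form limits depend on the arm sizes, the alpha of 0.05 and no affected controls. The simulated percentages also depend on normal changes with a common SD. The conclusion concerns the laboratory analysis, not the trial's safety surveillance as a whole. It should be corrected before the data are analysed, but it does not threaten the conduct of the trial.

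**What to change.** State in the statistical section that laboratory safety is analysed descriptively. For each analyte and arm, report:
- a shift table from baseline to day 90 (low, normal, high by the laboratory's reference range);
- the number and percentage newly out of range, with exact confidence intervals.

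Add a listing of participants with abnormal liver or kidney tests. Keep mean change as description, and draw no safety conclusion from t-test p-values.

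The cost is some wording and a few extra tables. The data are already collected, and no visit, test or clinical rule changes. The gain is descriptive: each case becomes visible whatever its size, but the trial is too small for a formal between-arm test of rare abnormalities.

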### Blinding

This is an open-label trial. Neither participants nor investigators are blinded due to the nature of the intervention.

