### Strategies to improve adherence to protocols

Participants will receive a compliance chart (see extended data) to track their daily intake of the RF and eye-drop usage. At each scheduled visit (30, 60, and 90 days), they will be required to return any empty or unused medication and eye-drop bottles, which will be counted to assess adherence. Regular check-ins via phone calls will be conducted to remind participants of follow-up appointments and dosing schedules (see extended data). During the baseline visit, each participant will be counseled on the importance of adherence, correct eye-drop instillation technique, and the potential benefits of completing the full intervention.

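### The primary analysis is labelled intention-to-treat but leaves out randomised participants who took no dose, and in this open-label trial that exclusion can depend on arm

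*Protocol article*

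**What the plan says.** All references are to the protocol article.

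- **Statistical methods, label:** "The primary analysis follows the intention-to-treat (ITT) principle".
- **Statistical methods, rule:** the same sentence goes on to define the set as "incorporating all randomized participants who have received at least one dose of the allocated intervention".
- **Statistical methods, per-protocol set:** "A per-protocol (PP) analysis will also be performed among participants who strictly adhere to the intervention", with the stated role of "serving as a sensitivity assessment to confirm the robustness of the results". The section also allows multiple imputation for data judged missing at random.
- **Randomization and Blinding:** the principal investigator confirms eligibility, the envelope is opened, and the principal investigator assigns the group. "This is an open-label trial", so participant and investigator both know the arm before any dose is taken.
- **Interventions, Table 1:** Group A is allocated standard of care. Group B is allocated standard of care plus RF twice daily and Shigru Pallava (SP) drops four times daily.
- **Strategies to improve adherence to protocols:** participants get a chart "to track their daily intake of the RF and eye-drop usage", and returned medication and bottles are counted at 30, 60 and 90 days. No measure of adherence to standard of care is named.
- **Plans to promote participant retention:** outcome assessments are attempted in participants who discontinue the intervention.

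**The concern.** The label and the rule disagree. An intention-to-treat set is fixed by randomisation; a set that also requires a first dose is fixed partly by what happens afterwards. In a double-blind trial a one-dose rule can often be defended, because failing to start is unlikely to depend on the assigned arm. That defence is not available here: the arm is known, and the two arms ask different things of the participant at the start. If those who decline to start differ in prognosis from those who do start, the primary comparison is no longer between the groups that were randomised.

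The rule also cannot be applied without a further decision, because the article does not say what counts as a dose of the allocated intervention in each arm. In an open-label trial that decision should not be left until outcomes have been seen.

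The per-protocol analysis does not remove the difficulty. If strict adherence is judged with the tools described, it is judged mainly on products that only Group B receives. Group B adherers would then be compared with a largely unselected Group A. Agreement between that result and the primary one would not show that the primary one is sound.

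**Working it through.** **1. The plan's own figure.** The Sample size section gives 50 participants, 20 control and 30 intervention, at 2:3. Check: 50 × 2/5 = 20 and 50 × 3/5 = 30. This reproduces. The article states no alpha, power, effect size, SD or non-starter rate, so there is no further figure to reproduce.

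**2. Who the dose rule removes, by reading of the word dose.**

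| Participant | Any part of the Table 1 regimen counts | Only RF or SP counts in Group B |
|---|---|---|
| Group A, takes standard of care | kept | kept |
| Group A, never starts standard of care | excluded | excluded |
| Group B, takes standard of care, neither add-on | kept | excluded |
| Group B, takes one add-on only | kept | kept |
| Group B, takes nothing | excluded | excluded |

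The readings differ only in the third row. Under the second reading the exclusion is likely to fall mainly on Group B.

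**3. Can Group A lose anyone?** The text points both ways. Concomitant care has participants continuing their standard medication, and the Discussion describes patients already on conventional care, which would make the rule almost automatic in Group A. The eligibility section speaks of newly diagnosed, untreated patients, who could fail to start.

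**4. Size of the effect of the dose rule (illustration).** Let f be the share of Group B excluded and D the outcome gap, in SD, between those excluded and those kept. The full Group B mean is the mean of those kept minus f × D, so excluding them shifts the between-group difference by f × D. Assume 2 to 4 of 30 never dose, none are lost from Group A, and D is 0.5 to 1.0 in the unfavourable direction.

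- Lower end: 2/30 × 0.5 = 0.033 SD.
- Upper end: 4/30 × 1.0 = 0.133 SD.
- Standard error at 20 v 30, in SD units: √(1/20 + 1/30) = 0.289.
- As a fraction of the standard error: 0.033/0.289 = 0.12 and 0.133/0.289 = 0.46.
- Chance of a false positive favouring the intervention, nominally 2.5% (assuming a two-sided 5% test): P(Z > 1.96 − 0.12) = about 3.3% at the lower end and P(Z > 1.96 − 0.46) = about 6.7% at the upper end.

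**5. Size of the effect of per-protocol selection (illustration).** Using the same formula, assume 6 to 12 of 30 are lost from Group B only and D is 0.25 to 1.0.

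- Lower end: 6/30 × 0.25 = 0.05 SD, or 0.17 standard errors.
- Upper end: 12/30 × 1.0 = 0.40 SD, or 1.39 standard errors.

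The potential distortion is larger here because more participants can fail strict adherence than can fail to take a single dose.

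**The case against.** **The mislabel could be called a wording matter.** The trial is declared exploratory, with no confirmatory test. Trial kits are issued at baseline to people who have consented, so few may fail to take even one dose. Participants who start and then stop stay in the set, and their outcomes are sought. This stands as a limit on size, but the rule still contradicts its label and governs the primary analysis.

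**A reader might infer that the dose rule drops patients from Group B only.** The documents do not support that. Table 1 makes standard of care the allocated intervention in Group A and part of it in Group B. An untreated Group A patient who never starts could be excluded. A Group B patient who declines one add-on has taken the other, and one who declines both but takes standard of care has arguably been dosed. What holds is that the exclusion can depend on arm.

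**A reader might take the 6.7% as the expected error rate.** It is the extreme corner of an assumed range. The non-starter rate, the size of the gap and its direction are not in the article, and the bias could run the other way.

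**On the per-protocol set**, the Statistical methods section does not restrict adherence to RF and SP; that is inferred from the adherence section. Thresholds and arm-specific rules are commonly left to a fuller document, so their absence is not criticised. The analysis is already secondary. What remains is the stated role, confirming robustness, which a set probably selected within one arm cannot fill.

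**Conclusion.** The contradiction is certain: the set called intention-to-treat is a modified intention-to-treat set. That the exclusion can depend on arm follows from open allocation and the different starting demands of the two arms. That it falls mainly on Group B is plausible but depends on an undefined term.

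The likely effect on the primary comparison is small if few fail to start: 0.03 to 0.13 SD against a standard error of 0.289 SD, under the assumptions in the working. This is a flaw worth correcting because the correction is nearly free, and not one that by itself undermines the trial. The per-protocol point is secondary. It rests on an inference about how adherence will be judged, though the distortion could be larger there.

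**What to change.** 1. In Statistical methods, define the primary set as all randomised participants, analysed in the group to which they were allocated, whether or not any dose was taken.
2. In Plans to promote participant retention, extend the planned off-treatment assessments explicitly to participants who never start. Where their outcomes are still missing, use the multiple imputation already allowed, under its stated missing-at-random condition.
3. If the sponsor prefers to keep the dose rule, call the set modified intention-to-treat and state what counts as a dose in each arm. This is the weaker option, because arm-dependent exclusion remains possible.
4. Describe the per-protocol analysis as supplementary, apply an adherence definition to both arms, and remove the statement that it confirms robustness.

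**Cost:** items 1 and 2 take a sentence or two, plus some effort to follow non-starters. The estimate may be slightly diluted if some never start. Item 4 is also a wording change, except that an adherence rule covering both arms needs some record of standard-of-care use, and the article names none. Recruitment is still under way, so the set can be fixed by amendment before the outcomes are analysed.

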### Plans to promote participant retention

Participants receive reminder phone calls and messages a week and a day before each scheduled follow-up visit. Those with scheduling conflicts are offered alternative appointment times to ensure flexibility. In cases where participants discontinue the intervention, the study team attempts to conduct outcome assessments such as measuring IOP, performing optical coherence tomography (OCT), and conducting VF tests to capture essential end-of-study
data.

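### Missing outcomes are left to an optional imputation with a weak stated basis, so the intention-to-treat analysis is not secured

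*Protocol article*

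**What the plan says.** All the analysis rules are in the protocol article under Statistical methods. The primary analysis is labelled intention-to-treat, "incorporating all randomized participants who have received at least one dose of the allocated intervention". The missing-data rule is a single sentence: data judged to be missing at random "may be addressed using multiple imputation based on observed participant characteristics". A per-protocol analysis is the only sensitivity analysis named.

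The tests are split by purpose. For change over time, "Within each group, repeated-measures analysis of variance (RM-ANOVA) or a suitable post-hoc test will be employed to analyze continuous variables". For the treatment effect, "Between-group comparisons will be performed using the unpaired t-test or its nonparametric alternatives as needed". On software, "All statistical analyses will be conducted using IBM SPSS Statistics (Version 29) or later".

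Two other sections bear on the point. Table 4 schedules visual field testing, RNFL thickness and IOP at screening, baseline and days 30, 60, 90 and 180, so most participants will have several values of each outcome. Under Plans to promote participant retention, the article states: "In cases where participants discontinue the intervention, the study team attempts to conduct outcome assessments". Collecting outcomes after treatment stops is therefore intended but not assured. Sample size gives 30 intervention and 20 control participants, with no allowance for dropout.

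**The concern.** An intention-to-treat label defines who belongs in the analysis, but it does not by itself say what is done when their outcomes are missing. Here that is left open in three ways.

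- **Imputation is optional.** It may or may not be done, and no fallback is stated.
- **The condition cannot be checked.** Observed data cannot establish that values are missing at random, so the trigger is a judgement. In an open-label trial where the principal investigator enters the data, that judgement could be made with results by arm in view.
- **The named basis is weak.** Participant characteristics are mentioned. The participant's own visual field, RNFL and IOP values at other visits, which would usually be the best predictors, are not, and neither is arm.

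At stake are precision, a possible pull of the estimate towards no difference, and, if loss is related to outcome, bias. Outcome-related loss is plausible: the discontinuation section allows treatment to be halted when IOP or optic nerve measures worsen, or for deterioration attributed to the study products, which only the intervention arm receives. The Discussion itself notes high dropout in other neuroprotection studies.

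**Working it through.** **Inputs.** From the article: 20 control and 30 intervention participants; follow-up at days 30, 60, 90 and 180. Assumed, because the article states no rate: 3%, 5% or 10% missing independently at each visit, or 10%, 20% or 30% missing at day 90. Also assumed: a true day-90 difference of 0.80 SD, since no effect size is given. The plan has no power calculation to reproduce; only the split can be checked: 50 × 2/5 = 20 and 50 × 3/5 = 30, as stated.

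**1. No imputation, between-group t-test at day 90.** With baseline complete, only the day-90 value is needed. The number kept is 50(1 − m), and the standard error is multiplied by 1/√(1 − m).

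| m per visit | Kept of 50 | SE multiplier |
|---|---|---|
| 3% | 48.5 | 1/√0.97 = 1.015 |
| 5% | 47.5 | 1/√0.95 = 1.026 |
| 10% | 45.0 | 1/√0.90 = 1.054 |

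At larger losses, two-sided 5% power for 0.80 SD falls from 78% (20 v 30) to 73% (18 v 27), 68% (16 v 24) or 61% (14 v 21) at 10%, 20% or 30% missing.

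**2. No imputation, within-group repeated-measures ANOVA.** The conventional form needs every analysed visit, so the fraction kept is (1 − m)^k, with k = 3 to day 90 or k = 4 to day 180.

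| m per visit | k = 3: control, intervention | k = 4: control, intervention |
|---|---|---|
| 3% | 18.3, 27.4 | 17.7, 26.6 |
| 5% | 17.1, 25.7 | 16.3, 24.4 |
| 10% | 14.6, 21.9 | 13.1, 19.7 |

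These losses affect the within-group analyses only.

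**3. Imputation without arm.** If a fraction f is missing in each arm and the imputed values have the same mean in both arms, the estimated difference is (1 − f)D + f × 0 = (1 − f)D. For D = 0.80 this gives 0.72, 0.64 and 0.56 at f = 10%, 20% and 30%.

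A simulation checked this: 1,000 runs, 20 imputations, values missing completely at random, day-60 effect two thirds of the day-90 effect, within-arm correlation 0.64 between those visits, and a baseline characteristic unrelated to outcome. Mean estimated differences for a true 0.80:

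| Approach | 10% missing | 20% | 30% |
|---|---|---|---|
| Available cases, no imputation | 0.81 | 0.79 | 0.78 |
| Characteristic only | 0.73 | 0.63 | 0.55 |
| Characteristic and day-60 outcome, no arm | 0.76 | 0.71 | 0.66 |
| Characteristic and arm | 0.81 | 0.79 | 0.78 |
| Characteristic, arm and day-60 outcome | 0.81 | 0.79 | 0.78 |

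Arm is what removes the shrinkage; an earlier outcome alone removes only part of it. The first row shows that dropping cases costs precision but does not bias the estimate when loss is unrelated to outcome.

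**The case against.** The strongest reply has four parts.

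**The arm comparison is not a completer analysis.** A reader might infer that repeated-measures ANOVA confines the treatment comparison to participants with every visit, giving at the assumed 3%, 5% or 10% about 44, 41 or 33 of 50 (50 × (1 − m)^4). The article does not support that. It assigns the ANOVA to change within each group and the arm comparison to an unpaired t-test, which needs only the compared visit, plus baseline for a change score. A day-90 value collected after treatment stops would be used even if days 30 and 60 are missing. This part stands in full.

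**Shrinkage is not inevitable.** A reader might also infer that imputation as described must pull the arms together. The wording neither includes nor excludes arm or earlier outcomes, and a model containing them fits the text. This also stands: shrinkage follows only from a characteristics-only reading, and case deletion and shrinkage are alternatives, not joint consequences.

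**The detail may sit elsewhere.** A condensed article can leave the imputation model to an analysis plan, so the absence of a full variable list is no fault. The objection here is to what the article does state: a discretionary rule, an untestable trigger, and a named basis that leads to the wrong answer if followed literally.

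**The remedy shares the assumption.** A mixed model also relies on missing at random. That is correct, and it is why a sensitivity analysis belongs with it. The trial's exploratory status lowers the stakes but does not make an open choice of method preferable.

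**Conclusion.** The point holds in a limited form. The article labels the primary analysis intention-to-treat but does not fix how missing outcomes enter it, and the tests it falls back on discard follow-up already collected.

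The size depends on a missing rate that the article does not give. Without imputation, the cost to the day-90 comparison is modest at the assumed 3% to 10% per visit: a standard error about 1.5% to 5.4% larger. Bias would need loss related to outcome, which is plausible here but not shown. With a characteristics-only imputation that omits arm, the expected shrinkage is about equal to the missing fraction, and including arm removes it. There is no outright contradiction with the intention-to-treat claim: one sentence defines the analysis set and the next offers a way to fill gaps in it. The weakness is that the offer is not a commitment. The wording should be changed before analysis.

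**What to change.** Make the primary between-arm analysis a likelihood-based mixed model using all observed visits of all randomised participants, with arm, visit, arm-by-visit interaction and baseline value as terms, and take the arm contrast at day 90 as the result.

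If multiple imputation is kept instead, commit to it and state that the imputation model includes arm, the baseline value and the outcome at the other visits. With only 20 controls, arm as a covariate may be more stable than imputing separately by arm.

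In either case add one delta-adjusted sensitivity analysis, in which imputed intervention-arm values are made progressively worse, because both approaches assume missing at random and the planned per-protocol analysis does not test that.

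The cost is a few sentences of statistical text and modest analyst time. The analyses are feasible in the planned SPSS software and need no new data. The Study status section reports recruitment as ongoing, so the change can still be made before analysis.
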